### Sensitivity Analysis

To calculate the robustness of our undiagnosed CKD definition (identified through 2 eGFR measures and no ICD-9/10 CKD diagnosis codes, and OHDSI ICD-10 CN2016 is used in the CRDS database), we will conduct sensitivity analyses 1-2 that assess whether the lack of healthcare encounters, as originally defined, truly captures an undiagnosed population.

Sensitivity analysis for undiagnosed CKD includes ICD-9/10 diagnosis codes for stage 3 CKD or higher

Sensitivity analysis for undiagnosed CKD includes ICD-9/10 diagnosis codes for CKD based on a broader definition derived by Winkelmayr *et al.*, 2005 ([section 8](#)). We will conduct sensitivity analysis 3 to assess if we have included sufficient individuals with undiagnosed CKD in the database, as required by study inclusion [criteria 2](#).

Sensitivity analysis for adjustment of inclusion criteria 2 from “at least 12 months of continuous presence in the database or registration in the data prior to the first qualifying eGFR (for data sources with information on enrollment)” to “at least one medical visit with diagnostic record within  $\leq 12$  months prior to the first qualifying eGFR”. There are no changes in any other inclusion and exclusion criteria. Analyze undiagnosed CKD according to the primary study definitions using eGFR measures captured within a specific time period prior to diagnosis.

- *Time to CKD diagnosis*

For the cohort of patients with no CKD diagnosis code as of the study index date (cohort 2), the median (95% CI) time in days/months from the study index date to physician-diagnosed CKD (using the primary CKD study definition) will be calculated using the Kaplan-Meier method. Survival times will be censored as of the last day of follow-up for patients who remain undiagnosed by a physician. Time to physician diagnosis of CKD will be calculated overall and by patient characteristics and comorbidities. If possible, association between baseline characteristics and time to CKD diagnosis will be assessed using relevant regression models. The time to physician diagnosed stage 3 CKD or higher (sensitivity analysis #1) and the time to CKD using a broader definition (sensitivity analysis #2) ([section 8](#)) will also be calculated.

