### CKD management and monitoring

To assess the current state of CKD management and monitoring practices by CKD diagnosis status, information on quality indicators will be extracted in the following seven domains starting 6 months post index date:

1. Detection and recognition of CKD (e.g. UACR testing within 6 months)
2. Monitoring of kidney function and complications (e.g. serum creatinine measurement within 18 months)
3. Use of recommended medications (e.g. ACEIs, ARBs or SGLT2i)
4. Kidney function monitoring after initiation of ACEIs ARBs
5. Kidney function monitoring after initiation of SGLT2i
6. Management of blood pressure
7. Monitoring of glycaemic control

**Statistical Analysis:** The prevalence of undiagnosed stage 3 CKD will be calculated. The prevalence numerator will include all patients who fulfill the undiagnosed stage 3 CKD case

definition at any time during the observation period. The denominator will include all individuals included in the study (cohort 1).

Prevalence will be estimated by dividing the numerator by the denominator, and 95% confidence intervals (CI) around prevalence will be estimated using a binomial distribution. Prevalence will be assessed during the observation period and by each calendar year of the index date. Prevalence will also be calculated among subgroups of patients based on age, sex, and the presence of key baseline comorbidities. For those with no CKD diagnosis code on or before the index date (cohort 2), time to CKD diagnosis will be assessed using KM curve.

Baseline characteristic (at index date) will be described for undiagnosed versus diagnosed CKD. The proportion of patients achieving each of the specified quality indicators will be described by CKD diagnosis status, overall and by comorbidities.

**Sample Size Estimation:** If the prevalence rate of undiagnosed CKD is between 60% and 80%, then a sample of 1,000 patients will be sufficient to estimate the prevalence rate with a margin of error of  $\pm 3\%$  in a 95% CI per institution/country (6% width of 95% CI).

According to the feasibility assessment of REVEAL-CKD in China, the number of patients who meet the inclusion and exclusion criteria in the Chinese Renal Disease Data System (CRDS) database is about 27,000 and the number of patients who met the inclusion and exclusion criteria of sensitivity analysis in the CRDS database is about 46,000^3.

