**Table 1. Study objectives**

| Primary objectives:                                                                                                                                                                                                                      | Outcome measure                                                                                                                                                                                                                                                                                                                                                                                                                          | Hypothesis tested (if relevant) |
|-------------------------------------------------------------------------------------------------------------------------------------------------------------------------------------------------------------------------------------------------|-------------------------------------------------------------------------------------------------------------------------------------------------------------------------------------------------------------------------------------------------------------------------------------------------------------------------------------------------------------------------------------------------------------------------------------------------|----------------------------------------|
| 
 
Describe the point prevalence of undiagnosed stage 3 CKD,
 
Describe time to CKD diagnosis in patients with no prior CKD diagnosis code at index date (time of second qualifying eGFR)
 
 | 
Point prevalence of undiagnosed CKD stage 3
 
Prevalence of undiagnosed CKD defined as proportion of: (1) Patients with eGFR 30–59 (inclusive) and no diagnosis code for CKD divided by (2) all patients with eGFR 30–59
 
It will be assumed that patients with at least one diagnostic code for CKD have diagnosed CKD
 
Median time to CKD diagnosis from index date. KM curve, overall and by patient characteristics
 | 
Not applicable
                  |

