### 3.3 Study Population

Patients  $\geq 18$  years old with two consecutive eGFR measurements indicating stage 3 CKD ( $\geq 30$  and  $< 60$  mL/min/1.73m^2 using CKD-EPI (preferred) or MDRD equation) recorded more than 90 days apart (max. 730 days), meeting the inclusion criteria will be included in the study and constitute the denominator for the calculation of the prevalence of undiagnosed stage 3 CKD. A subset of the study population will be identified with no encounters with a diagnosis code for CKD any time prior to the study index date (for primary objective 2). The observation period will vary based on the period of data coverage, which may be unique to each data source. In CRDS database observation start date will be January 1, 2015, and observation end date will be 31 December 2020.

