### **3.5 Participant Follow-up**

CKD diagnosis status will be assessed using data from the  $\geq 12$ -month baseline period until six months post-index for the calculation of undiagnosed CKD prevalence. To assess time to CKD diagnosis (primary objective 2), patients will be followed from the index date to the earliest of their follow-up end date (due to death or transfer out of database) or end of data coverage period

To assess CKD management and monitoring quality indicators (secondary objective 3), patients will be followed starting from the six months post index date until the follow-up end date (due to death or transfer out of the database) or end of data coverage, whichever comes first.

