#### **Primary objective**

- *Estimation of the prevalence of undiagnosed stage 3 CKD*

The prevalence numerator will include all patients who fulfill the undiagnosed stage 3 CKD case definition (see [section 4.2](#)) at any time during the observation period. The prevalence denominator will include all individuals meeting the inclusion criteria for this study (cohort 1). Prevalence will be estimated by dividing the numerator by the denominator, and 95% CIs around prevalence will be estimated using a binomial distribution. The denominator population should be the source of cases for the numerator. The prevalence of undiagnosed

stage 3 CKD (cohort 2) will be stratified according to patient subgroups of interest ([section 4.4](#)).

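### Time to CKD diagnosis (primary objective 2) is a Kaplan-Meier analysis that censors deaths, so read as an actual probability it overstates how many patients are diagnosed and how soon

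*Protocol*

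**What the plan says.** Primary objective 2 describes time to CKD diagnosis in patients without a CKD code at the index date.

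- **Outcome measure.** Table 1 gives it as "Median time to CKD diagnosis from index date. KM curve, overall and by patient characteristics".
- **Estimator.** Section 5.2 (Time to CKD diagnosis) says that the median time with its 95% CI "will be calculated using the Kaplan-Meier method".
- **Censoring.** The same paragraph says "Survival times will be censored as of the last day of follow-up for patients who remain undiagnosed by a physician". It has no separate rule for death.
- **End of follow-up.** Section 3.5 starts the clock at index and stops it at "the earliest of their follow-up end date (due to death or transfer out of database) or end of data coverage period".

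No section names a competing-risk estimator, and the limitations in Section 5.3.3 do not mention death.

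On who enters this analysis, Section 3.3 takes patients "with no encounters with a diagnosis code for CKD any time prior to the study index date", and the Study Population paragraph of the synopsis agrees with it. The Statistical Analysis paragraph of the synopsis instead reads "For those with no CKD diagnosis code on or before the index date (cohort 2"), and Section 5.2 describes cohort 2 as having no code as of the index date. In the prevalence paragraph of Section 5.2 the label turns up elsewhere: "stage 3 CKD (cohort 2) will be stratified according to patient subgroups of interest".

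**The concern.** Death is not loss to follow-up. Kaplan-Meier treats a censored patient as someone who could still be diagnosed later at the same rate as those who remain under observation. For a patient who has died that is impossible. One minus Kaplan-Meier then describes diagnosis in a population in which nobody dies, whereas a reader of a median time to diagnosis will take it as what happens to real patients.

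The protocol gives reason to expect that mortality matters. Section 1.1 describes CKD, even at stages 3A and 3B, as an independent risk factor for all-cause death. The curves are also to be shown by patient characteristics and comorbidities, and the subgroups in Section 4.4 include age, heart failure, anemia and established cardiovascular disease. If mortality differs between such strata, so does the overstatement.

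This is not a detail left open for a later analysis plan. The protocol itself fixes the estimator, the censoring rule and the summary for a primary objective.

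Separately, the wording on cohort 2 does not settle whether a patient first coded on the index day is excluded or is an event at time zero.

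**Working it through.** **The plan's own figures.** The protocol states no median, diagnosis rate, death rate or event count for this objective, so there is nothing to reproduce. Its one design calculation (1,000 patients, ±3% for a prevalence of 60% to 80%) concerns primary objective 1 and does not bear on this point.

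**Direction.** At each diagnosis time, both estimators add the observed diagnosis hazard multiplied by a survival factor. For one minus Kaplan-Meier, that factor falls only at diagnoses. For Aalen-Johansen, it falls at diagnoses and deaths. The second factor can never be larger than the first. One minus Kaplan-Meier is therefore never below the cumulative incidence, and it exceeds it once a death precedes a later diagnosis.

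**Size.** The rates are assumptions: diagnosis hazard h = 0.10 or 0.15 per year, death hazard d = 0.03 or 0.08 per year, both constant. At t = 4 years:

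- One minus Kaplan-Meier: 1 − exp(−4h)
- Cumulative incidence: h/(h+d) × [1 − exp(−4(h+d))]

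| h | d | 1 − KM | Cumulative incidence | Excess (points) |
|---|---|---|---|---|
| 0.10 | 0.03 | 33.0% | 31.2% | 1.8 |
| 0.10 | 0.08 | 33.0% | 28.5% | 4.5 |
| 0.15 | 0.03 | 45.1% | 42.8% | 2.3 |
| 0.15 | 0.08 | 45.1% | 39.2% | 5.9 |

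The first two rows also show the effect across strata. Two groups with the same diagnosis rate but different mortality give the same Kaplan-Meier curve (33.0%), although 31.2% of one group and 28.5% of the other are actually diagnosed.

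**Wider range.** With h from 0.05 to 0.30 and d from 0.02 to 0.15 per year, the excess is 0.0 to 1.8 points at 1 year, 0.4 to 10.0 at 3 years and 1.0 to 18.0 at 5 years.

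**Median.** With h = 0.15 and d = 0.05, the Kaplan-Meier median is ln 2 / 0.15 = 4.62 years. The cumulative incidence reaches 50% at −ln(1 − 0.5/0.75)/0.20 = 5.49 years.

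**Simulation check.** With 20,000 patients, h = 0.15, d = 0.05 and uniform administrative censoring up to 5.75 years, the 3-year estimates were 36.4% (one minus Kaplan-Meier) and 34.1% (Aalen-Johansen). The formulas give 36.2% and 33.8%.

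**Cohort 2.**

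| Place | Treatment of a code on the index day |
|---|---|
| Synopsis, Study Population; Section 3.3 | Not excluded |
| Synopsis, Statistical Analysis | Excluded |
| Section 5.2, Time to CKD diagnosis | Excluded, on the natural reading of *as of* |

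In the prevalence paragraph of Section 5.2, the denominator is stated to be cohort 1. One sentence later the cohort 2 label is attached to undiagnosed stage 3 CKD, which under Section 4.2 also requires no code up to 6 months after index. That is a different group from the patients with no code at index.

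**The case against.** The best defence is that the study is purely descriptive and that Kaplan-Meier with deaths censored answers a legitimate question: the rate of diagnosis among patients still alive, under the usual independence assumption. On that view cumulative incidence is not plainly better for comparing strata, because an older group can look less diagnosed simply because more of its members die. Cause-specific regression censors deaths too. This stands as far as it goes: Kaplan-Meier is valid for the cause-specific rate. But a median time to diagnosis is not normally read as a rate among survivors, and nothing in the protocol tells the reader to do so.

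It can also be said that the size is assumed, and that mortality capture is not among the minimum data criteria in Section 3.2. Both are true. They limit what can be said about size, not about direction.

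Three stronger inferences might tempt a reader, and the documents do not support them:

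- *The objective fails if the median is not reached.* The median is not the only summary. Table 1 and the synopsis also name the Kaplan-Meier curve.
- *Follow-up cannot exceed about 4.75 years, so a median needs a diagnosis rate of at least ln 2 / 4.75 = 0.146 per year.* This holds only if the 12-month lookback must begin on or after 1 January 2015, which the protocol does not say. Section 3.2 describes data from 1994 onwards. Without that restriction the longest follow-up is about 5.75 years, and the threshold is ln 2 / 5.75 = 0.121. Both thresholds also assume a constant hazard.
- *Stratified prevalence will be computed within cohort 2 and so be grossly inflated.* The same paragraph states cohort 1 as the denominator, so the label reads as a slip.

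**Conclusion.** The point holds for the death censoring. Sections 3.5 and 5.2 together treat death as ordinary censoring in the analysis of a primary objective. Read as the actual probability of diagnosis, the resulting curve overstates the proportion diagnosed and its median comes too early, with a larger error in high-mortality strata.

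The direction follows from the estimators themselves. The size does not come from the documents: 1.8 to 5.9 points at 4 years rests on assumed constant hazards of 0.10 to 0.15 (diagnosis) and 0.03 to 0.08 (death) per year, and at 1 year the excess stays below 2 points over the whole wider range.

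The cohort 2 wording is a minor, separate matter. A reader might infer that the risk set as a whole is undefined. It is not: the synopsis analysis paragraph and Section 5.2 essentially agree, and what remains is the treatment of index-day codes and one misplaced label. Neither contributes to the overstatement.

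**What to change.** 1. In Section 5.2, Table 1 and the synopsis, make the cumulative incidence of CKD diagnosis, with recorded death as a competing event (Aalen-Johansen), the main estimate for primary objective 2. Report it at fixed times such as 6, 12, 24 and 36 months with 95% CI, overall and by stratum, plus the median if reached.
2. Keep the Kaplan-Meier curve as supportive, described as reflecting the diagnosis rate among patients still alive. Use cause-specific hazards for the regression.
3. In the Study Population paragraph of the synopsis and in Section 3.3, change *prior to* the index date to *on or before* it, to match the synopsis analysis paragraph and Section 5.2.
4. In the prevalence paragraph of Section 5.2, correct the label on stratified prevalence from cohort 2 to cohort 1.

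The cost is wording and a modest amount of extra analysis in standard software, since death already ends follow-up under Section 3.5. The new estimate does depend on how completely deaths are recorded. The report should therefore give the number of recorded deaths and state that limit.

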### **Secondary objectives**

- *Trends over time*

Trends in the prevalence of undiagnosed CKD over time will be examined by calculating the prevalence during each calendar year of available data. Patients who have a second qualifying

eGFR measurement for stage 3 CKD (index date) during a given calendar year will contribute data toward the calculation of prevalence for that year. It is possible that some patients may contribute data as an undiagnosed stage 3 CKD case during one calendar year, and as a diagnosed stage 3 CKD case during a subsequent calendar year. However, once patients have a physician diagnosis of CKD, they cannot contribute data as an undiagnosed case during subsequent calendar years. It is also possible that some patients may have an initial diagnosis code for CKD that occurs <6 months following their qualifying eGFR, but in a subsequent calendar year. These patients should be classified as “diagnosed” during the year of their qualifying eGFR. In the same way, patients should be classified as “undiagnosed” during the year of their qualifying eGFR if their diagnosis code occurs >6 months following their qualifying eGFR in a subsequent calendar year.

- *Diagnosed versus undiagnosed CKD (baseline characteristics)*

Baseline characteristics will be summarized for diagnosed and undiagnosed CKD patients to compare relevant descriptive statistics and absolute standardized differences. A logistic regression model examining baseline factors associated with undiagnosed CKD will be conducted. The dependent variable is not having CKD diagnosed by a physician as previously described (e.g., presence vs. absence). Baseline characteristics as defined in [section 4.3](#) will be included in the model. Parameter estimates along with odds ratios, 95% C.I.s and p-values will be reported.

The proportions of patients receiving treatment for CKD (ACEi, ARB and SGLT2i) within 12 months following the study index date will be assessed for the diagnosed and undiagnosed CKD groups. Additionally, patients prescribed CKD treatments in absence of a code for hypertension and/or heart failure will be assessed. These analyses will help assess the clinical applicability of our methods to detect undiagnosed patients e.g., whether a significant proportion of patients without codes for CKD are being treated for the condition with medications indicated for other uses, e.g., HTN, HF.

- *Quality indicators*

The proportion of patients achieving each of the quality indicators will be calculated for diagnosed and undiagnosed CKD patients. Estimates will be stratified by patient subgroups (section 4.4). Estimates will be calculated separately for all patients as well as the subset with complete follow-up data during the specified interval over which the quality measure is to be assessed (for data sources with information on enrollment).

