## 2. OBJECTIVES AND HYPOTHESES

The overall aim of this study is to describe the prevalence and predictors of undiagnosed stage 3 CKD in priority countries.

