#### Inclusion criteria

1. At least two consecutive eGFR laboratory tests with values  $\geq 30$  and  $< 60$  mL/min/1.73 m^2 (Stage 3A or 3B) that are  $> 90$  and  $\leq 730$  days apart. The index date is the date of the second eGFR measure meeting the criteria for stage 3 CKD
2. At least 12 months of continuous presence in the database or registration in the data prior to the first qualifying eGFR (for data sources with information on enrollment)
3. Age  $\geq 18$  years at index date

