### **4.2 Outcomes**

#### **Case Definition – Undiagnosed Stage 3 CKD**

Patients with undiagnosed stage 3A-3B CKD will be identified if they have no healthcare encounter with a diagnosis code for CKD at any time during the  $\geq 12$ -month lookback period before the first eGFR measurement and up to 6 months post-index date (baseline period). Those with a documented diagnosis of CKD during this time period will be considered as having diagnosed CKD. It will be assumed that patients with at least one diagnostic code for CKD during the above specified time window have diagnosed CKD. 错误!未找到引用源。 below shows the study schematic.

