## 4.3 Other Variables and Covariates

The following baseline variables will be examined. Unless otherwise specified, medical history/comorbidity will be assessed using all available data prior to the index date. Baseline physiological and laboratory values will be extracted at the point of index date or using the most recent values during the 12 months before the index date. Similarly, medication use will be ascertained on or within 12 months before the index date.

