- Diabetes mellitus
  - Type 1 diabetes (T1D)
  - Type 2 diabetes (T2D)
  - Unclassified diabetes
- Hypertension
- Glomerulonephritis
- Hyperkalemia
- Hypertensive kidney failure
- Diabetic nephropathy
- Acute kidney injury (using diagnostics codes)
- Unspecified kidney disease
- Gout
- Poly cystic kidney disease
- Lupus
- Number of clinic visits in the year before the index date

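### The logistic model for undiagnosed CKD includes medications, visits and laboratory values that may follow the diagnosis, so their odds ratios cannot be read as predictors

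*Protocol*

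**What the plan says.** Section 2 of the protocol sets the purpose: "The overall aim of this study is to describe the prevalence and predictors of undiagnosed stage 3 CKD in priority countries".

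The model that bears on predictors is in section 5.2, under the secondary objectives: "A logistic regression model examining baseline factors associated with undiagnosed CKD will be conducted". Its covariates are fixed there as well: "Baseline characteristics as defined in [section 4.3](#) will be included in the model". Odds ratios, 95% confidence intervals and p-values are to be reported.

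The time points come from three other places:

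- **Time zero** (section 3.4): "The index date is the date of the second eGFR measure meeting the criteria for stage 3 CKD". The two measurements lie more than 90 and at most 730 days apart.
- **Outcome** (section 4.2): a patient is undiagnosed if no CKD code appears in the "lookback period before the first eGFR measurement and up to 6 months post-index date (baseline period"). Any code in that span makes the patient diagnosed.
- **Covariates** (sections 4.3 and 4.3.1): comorbidities come from all data before index, and laboratory values from index or the preceding 12 months. For drugs: "Similarly, medication use will be ascertained on or within 12 months before the index date". The list also has "Number of clinic visits in the year before the index date".

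Section 5.2 also plans time to diagnosis in cohort 2, the patients with no CKD code as of index. Kaplan-Meier estimates by patient characteristics and comorbidities are committed. A regression on baseline characteristics is to be done only if possible.

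**The concern.** A predictor of being missed must be measured before the patient is, or is not, diagnosed. In the section 5.2 model this order can be reversed for every diagnosed patient whose code came before index. Such a patient may have been given an ACE inhibitor, ARB or SGLT2 inhibitor, been seen more often, or had more laboratory tests because the diagnosis had been made. The model then reports treatment, visits or testing as factors that make a missed diagnosis less likely.

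The protocol itself treats several of these variables as results of diagnosis. Section 5.2 describes ACE inhibitors, ARBs and SGLT2 inhibitors as CKD treatment. Secondary objective 3 compares UACR testing, laboratory monitoring and drug use by diagnosis status as management outcomes. Section 5.1 gives missing baseline data a category of its own, so whether a test was done at all can enter the model too.

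At stake is the reading of the adjusted odds ratios. A reader who takes them as answering the section 2 aim could conclude that untreated or rarely seen patients are the ones missed, when part or all of that pattern is the effect of diagnosis on care.

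**Working it through.** **1. Order of events.** A code in the lookback precedes the first eGFR, and index follows that eGFR by more than 90 days. Such a code therefore precedes index by more than 90 days. If the two eGFRs are 365 to 730 days apart, it precedes the whole 12-month window for drugs, laboratory values and visits. Codes between the two eGFRs also count as diagnosed and also precede index. Only codes in the 6 months after index are sure to follow the covariates. Patients coded before index are a recognised group, since cohort 2 is defined by leaving them out (sections 3.3 and 5.2).

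**2. Overlap of codes.** Section 4.3.1 lists diabetic nephropathy and hypertensive kidney failure as comorbidities. The primary CKD definition in Table A1 includes diabetes with renal manifestation and hypertensive CKD. If the comorbidities are found with the same codes (their code lists are not in the protocol), a patient who has one is diagnosed by definition. The covariate then restates the outcome, and its coefficient can approach complete separation.

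**3. Illustrative size.** The protocol gives no figure for this bias. Its one calculated figure, 1,000 patients for ±3 points at 60% to 80% prevalence, reproduces (1.96 × √(0.6 × 0.4 / 1,000) = 3.04 points at worst) but does not bear on this point.

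Take a drug with no effect on being diagnosed. Let q0 be use without a code, q1 use after a code, and f the share of diagnosed patients coded early enough for the code to affect the drug record. All three are assumptions.

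- Use among diagnosed patients = f × q1 + (1 − f) × q0
- Odds ratio for undiagnosed = [q0 / (1 − q0)] ÷ [use / (1 − use)]

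From section 5.5: N = 27,000, with 60% undiagnosed (16,200 against 10,800). The confidence interval uses the standard error √(1/a + 1/b + 1/c + 1/d) of the log odds ratio from the two-by-two table. With q0 = 40%:

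| q1 | f | Use if diagnosed | Crude OR | 95% CI |
|---|---|---|---|---|
| any | 0 | 40.0% | 1.00 | 0.95 to 1.05 |
| 50% | 25% | 42.5% | 0.90 | 0.86 to 0.95 |
| 50% | 50% | 45.0% | 0.82 | 0.78 to 0.86 |
| 50% | 75% | 47.5% | 0.74 | 0.70 to 0.77 |
| 60% | 25% | 45.0% | 0.82 | 0.78 to 0.86 |
| 60% | 50% | 50.0% | 0.67 | 0.64 to 0.70 |
| 60% | 75% | 55.0% | 0.55 | 0.52 to 0.57 |

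At f = 90% and q1 = 60%, use is 58% and the odds ratio 0.667 / 1.381 = 0.48. With 80% undiagnosed the odds ratios are the same and the intervals slightly wider (0.85 to 0.96 in the weakest case). Except at f = 0, every interval excludes 1.

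**4. Events left in cohort 2.** Section 5.5 implies 20% to 40% diagnosed: 0.20 × 27,000 = 5,400 to 0.40 × 27,000 = 10,800. If 50% to 90% of them were coded before index (assumed), the number coded in the 6 months after index lies between 5,400 × 0.10 = 540 and 10,800 × 0.50 = 5,400.

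**The case against.** The strongest reply is that the model serves secondary objective 2, which is to describe characteristics at index by diagnosis status. The text speaks of associated factors, and sections 3.1 and 5.1 call the study descriptive. An association at index is a legitimate description. This stands for the cohort 1 comparison, but standardized differences already provide it. The regression adds an adjusted answer to a question about factors, and section 2 words that question as predictors.

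A reader might infer that the predictor aim goes unanswered altogether. The documents do not support that. Time to diagnosis by patient characteristics in cohort 2 belongs to primary objective 2, is committed without condition (Table 1, section 5.2) and has the right time order. It is unadjusted, and only the regression beside it is conditional.

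A reader might also infer that most diagnosed patients were coded before index, or that the model will return an odds ratio near those in the table. The protocol gives no split of codes before and after index. The table holds crude two-by-two odds ratios on assumed inputs, whereas the planned model adjusts for many covariates jointly.

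Three further limits stand. Age and sex cannot result from diagnosis, and many comorbidities predate it. A drug may have been started before a recent code or for another indication. Frequent visits can lead to a diagnosis as well as follow from one.

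**Conclusion.** The timing defect is in the protocol's own text and holds for covariates that a diagnosis can change: medications, visit counts and some laboratory values. Their odds ratios from the cohort 1 model cannot be read as predictors of undiagnosed CKD. Coefficients for age, sex and earlier comorbidities are not reversed in time, but they are conditioned on variables that may be. Covariates that share codes with the outcome add a separate defect, if the same codes are used. The limitations in section 5.3.3 mention none of this.

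The size is unknown. With no true effect, use of 40% rising to 50% or 60% after a code, and 25% to 90% of diagnosed patients affected, the crude odds ratio falls between about 0.9 and 0.5. The expected 27,000 patients would make such a bias look precise without reducing it.

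It would be wrong to extend the point to the primary prevalence estimate, which does not use this model, or to the Kaplan-Meier analysis in cohort 2.

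**What to change.** In section 5.2, make the adjusted regression in cohort 2 (no CKD code on or before index) a committed analysis and name it as the one used for predictors. The outcome can be time to diagnosis with censoring, or a CKD code within 6 months after index. The time-to-diagnosis form also handles patients with incomplete follow-up. Match the number of covariates to the number of diagnosed events.

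Keep the cohort 1 comparison for secondary objective 2 as descriptive or associational, with standardized differences. If a cohort 1 model is retained, limit it to age, sex and comorbidities dated before the first CKD code. Leave out medications, visit counts, laboratory values that diagnosis can change, and covariates that share codes with the outcome.

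No new data are needed, since cohort 2 is already defined. The cost is fewer diagnosed events: about 540 to 5,400 coded within 6 months under the assumptions above, and the lower end would not carry the full section 4.3 list. The question also narrows to patients still uncoded at index, so the results will not describe those diagnosed earlier.
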